#### Acupuncture treatment group

3.4.2

The Acu-treatment group is treated with acupuncture, in addition to the treatment for the usual care therapy group. A disposable sterilized needle made of stainless steel (0.2 mm × 30 mm, Spring Handle Needle, DONGBANG Medical Co, LTD) will be used for treatment. The acupuncture points for treatment are GB 29, GB 28, BL 38, ST 36, CV 3, SP 9, GB 34, ST 28, SP 10, and ST 34. All the acupuncture points were used on the TKR-operated side for 20 min. The reporting of this randomized study was based on the Standards for Reporting Interventions in Controlled Trials of Acupuncture (STRICTA). The Acu-treatment group will receive eight treatments (four sessions between 3 and 8 days after surgery and four sessions between 9 and 14 days after surgery) over 2 weeks. A licensed doctor of Oriental medicine with formal education in the field and over 5 years of clinical experience and acupuncture will perform acupuncture according to the intervention schedule proposed in the protocol.

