### Recruitment, randomization, blinding, and nonblinding

3.6

Advertisements for patient recruitment will be posted on the Catholic Kwandong University International St. Mary's Hospital bulletin boards, along with posters, banner advertisements and internet cafes. All advertisements will be run after IRB approval.

Individuals who have given written consent for participating in the study will be assigned a screening number in order of the outpatient visit at screening. Unblinded subinvestigators who do not influence the research results and analysis will refer to the randomization list that has been prepared by a commissioned professional statistician and will assign participation numbers. Participants will be allocated to the usual care group and the usual care plus acupuncture group at a ratio of 1:1. A block randomization table is generated by an independent statistician, and patients are assigned to one of two groups according to the randomization table. The screening numbers, randomization numbers, and initials assigned to each participant are used as subject identification codes to identify the participant until the end of the clinical trial.

The usual care used in this study is not a clinical investigation product and does not require allocation concealment, since it is administered to all the groups. Moreover, it is impossible to blind the investigator and the participant in each group due to the nature of the study intervention, which is based on the contact between the patient and the medical staff. Instead, the investigator maintains blinding to prevent bias in evaluating the participant. If the clinical trial is completed, all clinical report forms (CRFs) are collected, the database process is terminated, and unblinding will be performed if required for statistical analysis.

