#### Early termination or dropout

3.8.4

The early termination or dropout criteria are as follows:

1.Violation of the inclusion/exclusion criteria2.Withdrawal of consent for participation3.Adverse reactions (including serious adverse reactions)

Adverse reactions refer to undesirable and unintended signs, symptoms, or diseases and do not necessarily have a causal relationship with the interventions administered during a clinical trial. However, since the present clinical trial involves patients who underwent TKR, adverse reactions may be deemed symptoms or side effects caused by TKR at the discretion of the operating surgeon and principal investigator. Symptoms that the principal investigator deems as unassociated with the intervention of this clinical trial are not classified as adverse reactions that occur during this clinical trial.

4.Poor compliance (compliance below 70% in the final compliance assessment) or inability to comply5.Violation of the clinical trial protocol6.Other reasons deemed valid by the researchers7.Diagnosis of an infection in the recovery room

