#### General principle for statistical analysis

3.9.1

An intention-to-treat (ITT) analysis will be performed as the primary analysis for patients who receive acupuncture at least once. A per-protocol analysis will also be performed for participants who have completed the study after excluding dropouts.

For intergroup comparisons, an independent *t* test will be performed for continuous variables if normality is satisfied. If normality is not satisfied, the Wilcoxon rank-sum test, a nonparametric statistical technique, will be performed. For comparisons between different time points within each group, a paired *t* test or Wilcoxon signed rank test will be used. An analysis of covariance (ANCOVA) adjusted for covariant factors that show significant differences with respect to the baseline in each treatment group and the initial baseline outcomes will be additionally determined. For categorical variables, the chi-square test or Fisher's exact test will be used.

All statistical analyses will be two-tailed with a 5% significance level. The last observation carried forward (LOCF) method will be used to handle missing values. Multiple imputation or a regression analysis will be additionally used to examine differences in the results.

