###### Exceptions to the exclusion criteria for the economic evaluation

3.9.3.4.4

Participants who drop out or are excluded due to the treatment effects or adverse effects of acupuncture or due to the worsening of the disease will be subject to an economic evaluation as long as the evaluation is feasible. The economic evaluation will be continued for the following dropout cases due to treatment effects or adverse effects.Cases: Drop-out due to recovery or loss of symptoms during the treatment period, drop-out due to the adverse effects from a drug, and treatment-related drop-out deemed by our researchers as associated with the target disease or the treatment provided in this clinical trial due to the secondary occurrence of a disease (e.g., surgical site infections, etc).These exceptional cases will be included in the ITT analysis as there is a high possibility that the effect estimates will go missing during the study. The LOCF will again be used to estimate the missing values. However, in cases in which the missing pattern is not monotone, multiple imputation can be used to check the sensitivity.

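### Section 3.8.4 makes adverse reactions, low compliance and protocol violations grounds for study dropout, and nothing in the protocol keeps clinical outcomes coming from those patients

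*Protocol article*

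**What the plan says.** Section 3.8.4 gives one list of criteria for early termination or dropout. Withdrawal of consent stands in it beside adverse reactions of any seriousness, "Violation of the clinical trial protocol" and "Poor compliance (compliance below 70% in the final compliance assessment) or inability to comply". The same section lets attribution decide what counts: "Symptoms that the principal investigator deems as unassociated with the intervention of this clinical trial are not classified as adverse reactions". Section 3.6 says that "it is impossible to blind the investigator and the participant in each group".

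Four other places bear on what happens to these patients:

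- Section 3.9.1 uses LOCF for missing values, with multiple imputation or regression in addition. It also states: "A per-protocol analysis will also be performed for participants who have completed the study after excluding dropouts".
- Section 3.9.3.4.3, in the economic part, carries a dropout's last measurement to every visit still to come.
- Section 3.9.3.4.4 makes an exception: "The economic evaluation will be continued for the following dropout cases due to treatment effects or adverse effects". It covers recovery, adverse effects and treatment-related secondary disease, and does not name poor compliance or protocol violation. It places these cases in the intention-to-treat analysis, expects effect data to be missing, and fills them by LOCF.
- Table 1 schedules K-WOMAC at screening, V10 and FU2 only, and the compliance assessment at V10.

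**The concern.** An intention-to-treat comparison needs outcomes from patients who stop or fall short of the assigned treatment. If stopping treatment also ends follow-up, the missing values depend on how treatment went, and LOCF replaces them with scores from an earlier stage of recovery.

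The triggers are also unlikely to fall equally on the two arms. Section 3.4.2 says "The Acu-treatment group will receive eight treatments", so only that arm has sessions to miss and needling to react to. Whether an event is an adverse reaction depends on its being linked to the intervention, in a trial where allocation is known to investigator and patient.

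Safety is at stake as well as efficacy. It is one of the stated aims, and the Introduction names infection and reoperation as the worry about acupuncture after knee replacement. A patient taken out because of a reaction would miss the later adverse-reaction assessments (Table 1: FU1 to FU3) and laboratory tests (FU2 and FU3).

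**Working it through.** **1. The plan's own figure.** Inputs from section 3.3: difference 3.60; SDs 4.05 and 4.16; two-sided alpha 0.05; power 80%; 10% dropout.

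- Pooled SD = √((4.05² + 4.16²)/2) = 4.105.
- A two-sample t test (noncentral t) needs 22 per group (power 81.1%; 21 per group gives 79.2%).
- 22/0.90 = 24.4, rounded up to 25 per group.

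The stated 22 and 25 reproduce, so the sample size is not at fault. With 25 + 25 all contributing, power is 85.9%.

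**2. Which data each trigger removes.** This reads Table 1 and section 3.8.4 together and takes dropout to end clinical data collection.

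- *Adverse reaction, protocol violation or inability to comply before V10:* the only K-WOMAC on file is the preoperative one. LOCF gives V10 change = screening − screening = 0. FU2 is also lost.
- *Compliance below 70%:* this is judged at V10, where K-WOMAC is also measured. The primary comparison in section 3.9.3.1 (screening to V10) is kept. FU1 to FU3 are lost, including the FU2 K-WOMAC and late safety data.

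If compliance is counted in acupuncture sessions (an assumption, since the article does not define it), 0.70 × 8 = 5.6. Then 5 sessions (62.5%) fail and 6 (75%) pass.

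**3. LOCF illustration for the primary comparison.** Assume that dropouts before V10 occur in the acupuncture arm only, that the control change is about 0, that every acupuncture patient would have had the full 3.60 benefit, and that the SD is unchanged. The estimated difference is 3.60 × (1 − d/25) for d dropouts:

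| Dropped of 25 | Difference | Power |
|---|---|---|
| 0 | 3.60 | 85.9% |
| 2 | 3.31 | 79.8% |
| 3 | 3.17 | 76.2% |
| 5 | 2.88 | 68.1% |

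Five is 10% of 50, that is, the whole dropout allowance falling in one arm.

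**4. Why the direction is open.** Let the control change at V10 be c (positive = worse than before surgery) and the dropped share of the acupuncture arm be p. The other assumptions are as in step 3. The estimated benefit is c − (1 − p)(c − 3.60) = (1 − p) × 3.60 + p × c. With p = 5/25 = 0.20 this is 2.88 + 0.20c:

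- c = −3.60 gives 2.16
- c = 0 gives 2.88
- c = 3.60 gives 3.60
- c = 7.20 gives 4.32

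These values of c are chosen for illustration. LOCF understates the benefit when c is below 3.60 and overstates it when c is above. The document does not say where patients will stand at V10 relative to their preoperative score.

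**5. Per-protocol (completer) analysis.** Assume no true effect, dropouts in the acupuncture arm only, and a correlation r between dropping out and poor response. The false difference is r × φ(z_p)/(1 − p) × 4.105, where φ is the standard normal density and z_p its p-quantile.

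- 2 dropped (p = 0.08): 0.20 points at r = 0.3 to 0.66 at r = 1.0; the nominal 5% error becomes about 5.3% to 8.5%.
- 5 dropped (p = 0.20): 0.43 to 1.44 points; about 6.4% to 20.7%.

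Here the error favours acupuncture, because poor responders are assumed to leave.

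**The case against.** **That clinical outcomes stop is an inference.** Section 3.8.4 does not say so, the sentence carrying values to all later visits stands in the economic section, and a full protocol may describe follow-up after discontinuation. This is fair as a caution. But the article does state the dropout list, contrasts completers with dropouts, and writes an exception for the economic evaluation alone. All three point the same way, and no text points the other way.

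A reader might also infer more than the documents support:

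- *That the 70% rule distorts the primary comparison.* It is applied at V10, where the primary K-WOMAC is taken. It can reach K-WOMAC only at FU2, and no K-WOMAC is scheduled at week 12.
- *That acupuncture will look better than it is.* This may happen in the completer analysis if poor responders leave. LOCF can go either way (step 4).
- *That the bias has a definite size, such as the dropped share times an assumed gap between dropouts and completers.* That is the bias from deleting patients. The main analysis keeps them and fills values by LOCF.
- *That only acupuncture patients can be dropped.* Usual care includes scheduled physiotherapy and drugs, compliance is not defined as sessions, and Table 1 does not restrict its assessment to one arm. Section 3.8.4 also says an adverse reaction need not be caused by the intervention. The roughly two-week hospital stay should limit missed sessions. The triggers are likely to be unequal, not confined to one arm.
- *That dropouts are still contacted for quality of life.* Section 3.9.3.4.4 continues the economic evaluation where feasible and expects effect data to be missing. Costs within the institution come from electronic records, which needs no contact.

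Section 3.6 also says that evaluation is kept blind. It does not say that the attribution of reactions is. Multiple imputation or regression is planned only as an addition and does not recover observations never made.

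**Conclusion.** The point holds as a defect in the dropout rule. Followed as written, it loses clinical outcomes for reasons tied to treatment and tolerability, probably unequally between arms, and it gives up late safety data in patients who had a reaction. Removal before V10 affects the primary comparison by setting the change to 0. The 70% rule affects only the later visits.

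Neither the direction nor the size of the bias can be settled from the document. The shrinkage from 3.60 to between 3.31 and 2.88 rests on 2 to 5 dropouts before V10, all in the acupuncture arm, with a control change near 0. Other assumptions move it up or down, and dropout balanced in number and prognosis would bias the completer comparison little. This should be corrected, but it does not invalidate the design.

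**What to change.** Split section 3.8.4 into two lists:

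1. Reasons to discontinue study treatment, with the clinical criteria left unchanged.
2. Reasons to end data collection, limited to withdrawal of consent to follow-up and loss to follow-up.

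State that all randomised patients are followed for the outcomes and adverse reactions that Table 1 schedules at each visit, whatever treatment they received. No assessment outside Table 1 is needed: FU1 stays a telephone contact, K-WOMAC stays at V10 and FU2, and the fall tests stay at V10 and FU3. Use the 70% rule only to define the per-protocol set, and bring sections 3.9.1, 3.9.3.4.3 and 3.9.3.4.4 into line.

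The cost is a change of wording and a few more completed assessments at visits already scheduled.

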**Methods/design::**

This is an open-label, parallel, assessor-blinded randomized controlled trial that includes 50 patients with TKR. After screening the patients and receiving informed consent, the patients are divided into two groups (usual care + acupuncture group and usual care group); the patients will then undergo TKR surgery and will be hospitalized for 2 weeks. The patients will receive a total of 8 acupuncture treatments over 2 weeks after surgery and will be followed up at 3, 4, and 12 weeks after the end of the intervention. The primary outcome is assessed using the Korean version of the Western Ontario and McMaster Universities Arthritis Index (K-WOMAC), and the secondary outcome is measured using the Numerical Rating Scale (NRS), Risk of Fall, and Range of Motion (ROM). Moreover, the cost per quality-adjusted life years (QALYs) is adopted as a primary economic outcome for economic evaluation, and the cost per NRS is adopted as a secondary economic outcome.

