The patients visited the hospital five times for evaluation. The screening (Visit 1, V1) included only those participants who submitted the informed consent form. For screening, the demographic information, medical history, physical examination, vital signs, questionnaire survey, laboratory test, and selection/exclusion criteria will be evaluated. Randomization and group allocation will be performed at screening. Fifty patients were enrolled and randomly divided into two groups. Patients who have passed the screening test will have a TKR and will be hospitalized in ∼2 weeks with usual care or usual care plus acupuncture therapy.

The patients will receive a total of eight acupuncture treatments over 2 weeks after surgery (four sessions between 3 and 8 days after surgery and four sessions between 9 and 14 days after surgery). They will be followed up at 3, 4, and 12 weeks after the end of the intervention. The primary outcomes will be assessed at V1, V10, and Week 4 of follow-up. The safety evaluations include adverse reaction evaluations, vital sign assessments, and laboratory tests. The adverse reaction evaluation will be performed every day during the hospitalization period and continued during follow-up at 3, 4, and 12 weeks after surgery. The vital sign assessment will also be performed daily during the hospitalization period after surgery and at 4 and 14 weeks of the follow-up. Laboratory tests will be performed during screening, at V5 and V9, and at 4 and 12 weeks of follow-up. An economic evaluation will be performed during the treatment period (2 weeks) and at 4 and 12 weeks after surgery and will investigate medical costs and utility (quality of life) to estimate the quality-adjusted life years (QALYs). The Euro-Qol five dimension scale (EQ-5D), a multiattribute health measurement instrument, will be used to assess the quality of life at baseline (Week 1) and at 2 and 4 weeks. Medical costs will also be investigated at baseline (week 1) and at 2, 4, and 12 weeks for a total of four assessments. These evaluations are performed simultaneously with the clinical trial through in-person interviews during the survey period and through in-person interviews, phone calls, and online communication using questionnaires thereafter according to a predefined arrangement with the patient.

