#### Exclusion criteria

3.5.2

The following patients are excluded from participating in the trial:

1.those who had undergone total knee arthroplasty due to gout;2.those who had total knee arthroplasty due to trauma;3.those who had total knee arthroplasty due to autoimmune-related diseases such as rheumatoid arthritis;4.those who were participating in other clinical trials;5.those who had a history of participating in other clinical trials within 1 month;6.those who had difficulty writing a research consent form; and7.those who were judged to be inappropriate for the clinical study by the researchers.

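### Randomisation at screening precedes surgery, so patients dropped before the first acupuncture session have been randomised but fall outside both analysis sets

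*Protocol article*

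**What the plan says.** **Timing of allocation.** Protocol article, section 3.2: "Randomization and group allocation will be performed at screening". Table 1 ticks randomisation at V1 only. The abstract gives the same order: after allocation, "the patients will then undergo TKR surgery and will be hospitalized for 2 weeks". Table 1 places V1 one to seven days before V2, and V2, the first acupuncture visit, on postoperative day 3 ± 2.

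**Reasons for dropping a patient.** The list in section 3.8.4 includes:
- item 1: "Violation of the inclusion/exclusion criteria"
- item 6: "Other reasons deemed valid by the researchers"
- item 7: "Diagnosis of an infection in the recovery room"

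Item 1 refers back to criteria whose last exclusion (section 3.5.2, item 7) covers "those who were judged to be inappropriate for the clinical study by the researchers".

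**Who knows the arm.** Section 3.6 says "it is impossible to blind the investigator and the participant in each group", and shortly afterwards that "the investigator maintains blinding to prevent bias in evaluating the participant". Section 3.8.4 does not say who decides items 1, 6 and 7, or whether that person knows the arm.

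**Analysis sets.** Section 3.9.1 calls its primary analysis intention-to-treat but confines it to patients with at least one acupuncture session. The per-protocol set is the completers, without dropouts. Missing values are carried forward from the last observation.

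**The concern.** Between V1 and V2 a patient is already randomised, undergoes surgery, and can be dropped for reasons unrelated to the treatment under test. Had allocation waited until V2, these patients would simply not have entered the trial. As the plan stands, they enter and are then lost.

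Two things are at stake. The first is precision: each such loss uses up the dropout allowance on someone who never reached the comparison. The second is the comparison itself. Items 1 and 6 leave room for judgement, the arm is known from V1, and no blind decision is required. If such judgements fell differently in the two arms, the remaining patients would no longer be a randomised comparison. Listing these reasons for withdrawal is common and does little harm when everyone randomised is analysed. It matters here because section 3.9.1 does not analyse everyone randomised.

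**Working it through.** **1. Where a patient dropped before V2 ends up**

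| Set | Condition | Dropped between V1 and V2 |
|---|---|---|
| Primary (3.9.1) | at least one acupuncture session | out: no session before V2 |
| Per-protocol (3.9.1) | completed, dropouts left out | out |
| Economic evaluation (3.9.3.4.1) | took part at least once from V2 | out |

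Taken literally, the primary condition cannot be met by anyone in the usual-care arm. The kindest reading is at least one postoperative treatment visit in either arm. That reading still leaves out a patient dropped before V2.

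Section 3.9.3.4.4 keeps some treatment-related dropouts, with surgical site infection as an example, in the intention-to-treat analysis. It belongs to the economic evaluation, whose population starts at V2, so it does not clearly rescue these patients.

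Carrying values forward does not help either. K-WOMAC is measured at V1, V10 and week 4 (Table 1). A patient removed before V10 has only the preoperative score, so the imputed change is zero.

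**2. The plan's sample size, reproduced**

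Inputs from section 3.3: difference 3.60; SDs 4.05 and 4.16; two-sided α 0.05; power 80%; 10% dropout.

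- Pooled SD = √[(4.05² + 4.16²)/2] = √16.854 = 4.105.
- Noncentrality at 22 per arm = 3.60 / (4.105 × √(2/22)) = 2.91 on 42 degrees of freedom. The power is 0.811, and 22 is the smallest number per arm that reaches 80%.
- 22 / 0.90 = 24.4, rounded up to 25 per arm, 50 in total. This agrees with the protocol.

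**3. Cost in precision**

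Spare patients per arm: 25 − 22 = 3. Each loss uses 1/3 of that; two losses are 2/25 = 8% of an arm. With the same difference and SD, and with the numbers lost as assumptions:

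| Analysed per arm | Power |
|---|---|
| 25 v 25 | 0.859 |
| 22 v 22 | 0.811 |
| 20 v 20 | 0.771 |
| 19 v 19 | 0.749 |

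**4. Ceiling on bias**

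Simulation with no true effect, 25 per arm and SD 4.105, removing the k worst outcomes from one arm only:

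| k removed | Shift in difference (points) | Two-sided type I error |
|---|---|---|
| 1 | 0.33 (0.08 SD) | 6.6% |
| 2 | 0.62 (0.15 SD) | 9.4% |
| 3 | 0.88 (0.22 SD) | 13.3% |

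This is a worst case and not a forecast. It assumes that removal tracks the final outcome perfectly and happens in one arm only. Before V2 nobody has seen a postoperative K-WOMAC score, so real selection could follow prognosis only loosely.

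**The case against.** The strongest reply is that withdrawal is not the same as exclusion from analysis. Section 3.8.4 does not say that dropped patients leave the primary analysis. Under section 3.9.1 a patient dropped after one acupuncture session stays in it. That stands, and it confines the harm to the primary comparison to patients lost before V2, acting through the wording of section 3.9.1.

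Three stronger readings are tempting, and the protocol does not support them.

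- *Staff who know the arm may use the open exclusion criterion at any time to remove patients.* Section 3.2 has eligibility assessed at screening, and a violation most naturally means a patient who failed a criterion at that point. Late use of the clause is an inference. So is the decision-maker: section 3.8.4 names none, and section 3.6 is inconsistent about the investigator's blinding. The explicit open discretion after allocation is item 6.
- *The recovery-room infection rule is an eligibility criterion that biases the comparison.* Infection is not among the inclusion or exclusion criteria. Both arms have the same surgery and neither has had acupuncture by then, so its occurrence should not depend on arm.
- *Late randomisation would cost no patients.* Those who fail before V2 must still be replaced.

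It is also fair to say that the 10% allowance exists to absorb losses, and that the drop from 0.811 to 0.771 at 20 per arm is modest.

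**Conclusion.** The point holds in a limited form. Because allocation precedes surgery, any patient dropped between V1 and V2 is randomised and then appears in neither clinical analysis set as worded. The cost in precision can be bounded: three spare patients per arm, with power falling below 80% once an arm-balanced loss exceeds three each.

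The selection risk comes from the discretionary reasons, chiefly item 6 and any judgement involved in item 1. No decision blind to arm is required, in a trial that says its investigator cannot be blinded. Its size is unknown: the protocol gives no rate of infection, late ineligibility or discretionary removal. The type I error figures are only an upper illustration. The conclusion rests on reading section 3.9.1 as written; an analysis of everyone randomised would remove most of the harm.

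The change should be made, because the losses are avoidable and the remedy is cheap. Whether treatment should stop after an infection is a clinical matter and is not judged here.

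**What to change.** 1. Keep consent, the eligibility check and the preoperative baseline at V1. Issue the randomisation number after surgery, immediately before the first session at V2, in both arms. Align the abstract, Table 1, section 3.2 and section 3.6.
2. In section 3.9.1, define the primary set as all randomised patients, analysed as allocated. Keep them in follow-up whatever the section 3.8.4 reason, except where consent to follow-up is withdrawn. Exclusions for those reasons then apply only to the per-protocol set.
3. In section 3.8.4, state that ineligibility found after randomisation is judged by someone blind to arm, on facts that existed before randomisation. Require the reason for every removal to be recorded and reported by arm, including removals under item 6. Separate stopping treatment, a clinical decision, from leaving follow-up.

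If randomisation has to stay at V1, steps 2 and 3 are the minimum.

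**Cost.** No extra visit or test for a participant; several passages to reword and the randomisation tick to move. The acupuncturist has shorter notice. Patients lost before V2 no longer count towards the 50, so others must be consented and screened in their place.
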